**Figure 4 figure4:**
[figure not shown]
The neural signature of limitations in CdF and unique gait-related electroencephalographic activation. CdF: complex daily function; med.: medial; pert.: perturbed; PP: posterior parietal; SM: sensorimotor; unpert.: unperturbed; V.: visually.

## Results

### Aim 1—Establish the Neural Signature of CdF

#### Overview

Figure 4 shows individuals with and without the unique grEEG pattern and associations with mild complex daily functional limitations measured with ADL-PI [8,79]. A score of 100% in Figure 5 indicates all activities are performed without difficulties. In both walking tasks, individuals with the unique grEEG pattern expressed nominally more difficulties performing complex daily activities.

**Figure 5 figure5:**
[figure not shown]
Analysis pipeline for separating brain activity from non–brain related artifacts during MoBI recording. ERSP: event-related spectral perturbation; IC: independent components; ICA: independent component analysis; LH: left heel strike; LTO: left toe off; MoBI: mobile brain body imaging; RH: right heel strike; RTO: right toe off.

#### Walking Tasks

Participants will familiarize themselves with walking on the treadmill and are asked to determine their preferred walking speed before starting the experiment. For the VPW, participants will perform 4 visual perturbed and 4 unperturbed walking blocks randomized within participants. During perturbed stimulation, a large-scale visual field of dots is projected centrally onto a black wall in front of the participant. The stimulation consisted of 200 randomly placed white dots emanating outward from a central area of expansion. Superimposed to the outward motion is a sinusoidal perturbation in the mediolateral direction. A static image of dots placed randomly across the visual field serves as a control condition (ie, unperturbed walking). For the DTW, participants will perform the Go/No-Go task standing (4 blocks) and walking (4 blocks). Blocks are randomized within participants. The Go/No-Go stimuli consist of images from the International Affective Picture System [80]. Participants were instructed to click a wireless computer mouse button with the right hand each time a new image appeared (Go trials) but to withhold their response if the same image was shown twice in a row (No-Go trials). Each block consists of 180 trials and the probability of Go and No-Go trials will be 0.85 and 0.15, respectively. They will also walk wearing a safety harness.

#### Kinematics Recordings

The Optitrack infrared motion capture system with 9 cameras is used to collect kinematic data in the X/Y/Z direction at a sample frequency of 100 Hz (Arena version 1.5 acquisition software, Natural Point).

#### Electrophysiological Recordings

Continuous electroencephalography is recorded with a 64-channel BioSemi ActiveTwo system (digitized at 512 Hz; 0.05 to 100 Hz passband, 24 dB/octave). Data are high-pass filtered at 2 Hz and an automatic channel rejection procedure [81] is applied to exclude noise channels followed by visual inspection. Time-synchronized acquisition of electroencephalographic and motion tracking is conducted with Lab Streaming Layer software (Swartz Center for Computational Neuroscience, University of California San Diego).

#### Prevalence of Unique grEEG Activation

To estimate the prevalence of grEEG abnormalities in aging, we reanalyzed previously published data [16]. Using event-related potentials measured in control participants (ie, young adults), we defined a threshold (1.5 SD from the mean 2.2 µV) to calculate the percentage of unique grEEG (event-related potential, ERP_young_>1.5 SD, mean 2.2 µV) in older participants. The prevalence of grEEG abnormality in older adults was 25% (4 out of 16).

#### Data Analysis

##### Gait Kinematics

Spatiotemporal features of gait kinematics are determined by computing the velocity profile for each foot (for a detailed description, see De Sanctis et al [19]).

##### Integrated Gait-Electroencephalographic Analysis

Figure 5 shows the basic steps to identify or correct artifacts and model spatially resolved brain dynamics tied to the gait cycle that we apply in our proposal. We have validated and applied this analysis pipeline in prior work [12,15,61]. Independent component (IC) analysis will be used to parse electroencephalographic signals into ICs. The resulting ICs are source-localized using inverse source modeling [82,83]. Only dipoles located within the brain, with a fit accounting for at least 80% of the variance for a given IC scalp projection, are retained [84,85]. Cortical IC clustering will be used to cluster brain ICs across subjects using feature vectors coding for IC differences in power spectral density, dipole location, and scalp projection [86,87]. Event-related spectral perturbations (ERSPs) are computed from single trial spectrograms for each IC, time-locked to the right heel strike [88]. ERSPs are computed by determining the power spectra over a sliding latency window and normalizing the spectrogram by their respective mean spectra (averaged across the latency window) [88]. To average across all strides taken and compute gait cycle ERSPs, we time-warped single trial spectrograms applying a linear interpolation function to align left toe off, left heel strike, right toe off, and right heel strike across epochs following the methods introduced by Gwin and colleagues [87].

#### Statistical Plan Aim 1

##### Primary Analyses

grEEG measures will be compared between individuals with and without limitations in CdF using the 2-sample *t* tests to assess which grEEG measure is associated with limitations in CdF. Pearson correlation will be computed between grEEG measures and CdF scores.

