**Objective:**

Our goal is to establish the neural signature of decline in CdF during the preclinical dementia period.

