**Results:**

We provide preliminary findings showing that older adults reporting CdF limitations can be characterized by a unique gait-related neural signature: weaker sensorimotor and stronger motor control activation. This subsample also had smaller brain volume and white matter hyperintensities in regions affected early by dementia and engaged in less physical exercise. We propose a prospective observational cohort study in cognitively unimpaired older adults with and without subclinical AD (plasma amyloid-β) and vascular (white matter hyperintensities) pathologies. We aim to (1) establish the unique grEEG activation as the neural signature and predictor of decline in CdF during the preclinical dementia period; (2) determine associations between dementia-related pathologies and incidence of the neural signature of CdF; and (3) establish associations between a dementia risk factor, physical inactivity, and the neural signature of CdF.

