### Hypothesis

Our overarching hypothesis illustrated in Figure 1 is that the presence of dementia-related pathology during the preclinical period of dementia is associated with a unique gait-related electroencephalographic (grEEG) pattern that predicts a subsequent decline in CdF. The first aim of this study is to establish the neural signature of CdF. Our preliminary findings show that individuals reporting CdF limitations can be characterized by weaker pre as well as postcentral gyrus and stronger fronto-medial activation during complex gait (eg, dual-task walking). This unique grEEG activation pattern (neural signature) will predict CdF decline longitudinally. Our second aim is to determine the association of dementia-related pathology with the incidence of the neural signature of CdF in individuals without the neural signature at baseline. Specifically, we hypothesize that plasma-based assays of Aβ, T, and white matter hyperintensities (WMH) at baseline will independently and in combination predict the incidence of the neural signature of CdF. We also need to understand if and how behaviors are known to increase dementia risk (eg, physical inactivity) and may modify the neural signature of CdF as a prelude to developing interventions. Our third aim is to determine whether physical inactivity is associated with the prevalence and incidence of the neural signature of CdF in our sample.

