##### Longitudinal Analyses

The time-to-event analyses including Kaplan-Meier survival curves, log-rank tests, and Cox proportional hazards regression models will be used to assess whether unique grEEG patterns predict a decline in CdF longitudinally.

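### Aim 1 has a signature part and a prediction part, but its primary label covers only the cross-sectional signature part, and the hazard ratio quoted for the prediction test is not attainable with 180 people

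*Protocol article*

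**What the plan says.** The abstract gives the objective as follows: "Our goal is to establish the neural signature of decline in CdF during the preclinical dementia period". It words Aim 1 as to "establish the unique grEEG activation as the neural signature and predictor of decline in CdF during the preclinical dementia period". The Hypothesis section states the aim in two steps. First, "The first aim of this study is to establish the neural signature of CdF"; then the pattern "will predict CdF decline longitudinally".

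Statistical Plan Aim 1 has three parts:

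- **Primary Analyses.** "grEEG measures will be compared between individuals with and without limitations in CdF using the 2-sample" t test, these being "tests to assess which grEEG measure is associated with limitations in CdF". In addition, "Pearson correlation will be computed between grEEG measures and CdF scores".
- **Longitudinal Analyses.** Kaplan-Meier curves, log-rank tests and Cox models are to "assess whether unique grEEG patterns predict a decline in CdF longitudinally".
- **Power Analysis.** For the t test: 54 of 180 people with limitations, 80% power for 0.5 SD, two-sided 5%. For decline by grEEG pattern: a minimum detectable hazard ratio of 1.52 to 1.69, event rate 0.30 to 0.48, power 0.8, two-sided 5%.

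Table 1 lists the grEEG signature as the Aim 1 independent variable and the ADL-PI as its primary outcome, assessed yearly. Statistical Plan Aim 2 places its time-to-event analysis under Primary Analyses.

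**The concern.** Half of Aim 1 is a claim about the future: people with the pattern now will decline later. The analyses that carry the primary label cannot address that half. A difference in grEEG between people with and without limitations, or a correlation with CdF scores, leaves the order in time unknown, because the pattern may precede the limitation, follow it, or share a cause with it.

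As labelled, Aim 1 could be positive on its primary analysis while the time-to-event result is null, and the text does not say what could then be concluded. What follow-up adds to the cross-sectional preliminary findings is the evidence on decline, and that evidence has no primary status. If it is to carry the prediction claim, its power statement also has to be sound.

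**Working it through.** **1. Aim against analysis**

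| Part of Aim 1 | Analysis that addresses it | Labelled primary? |
|---|---|---|
| Establish the signature of CdF | t test, Pearson correlation | Yes |
| Show that the signature predicts decline | Kaplan-Meier, log-rank, Cox | No |
| Aim 2, for comparison: pathology predicts incident signature | Time-to-event | Yes |

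The two prospective claims are labelled differently. The primary t test also turns Table 1 round: CdF limitation forms the groups and grEEG becomes the response.

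**2. Power of the t test**

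Inputs from the Aim 1 Power Analysis: 54 with limitations, so 180 − 54 = 126 without; two-sided 5%; 80% power.

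- Standard error in SD units: √(1/54 + 1/126) = 0.1627.
- Detectable difference: (1.960 + 0.842) × 0.1627 = 0.456 SD (0.458 with the t distribution).
- Power at 0.5 SD: 86.4% with the t distribution.

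The stated 0.5 SD at 80% is thus slightly conservative.

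**3. Detectable hazard ratio for decline**

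Formula (Schoenfeld): HR = exp[(1.960 + 0.842) / √(D·p·(1 − p))], where D is the number of events and p the share with the pattern.

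- D = 180 × 0.30 = 54, or 180 × 0.48 = 86.4.
- p is not stated for Aim 1. Assumed range: 0.25 (the prevalence of grEEG abnormality given in the article, 4 of 16) to 0.50 (the most favourable value).

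| p | D = 54 | D = 86.4 |
|---|---|---|
| 0.50 | exp(2.802/√13.5) = 2.14 | exp(2.802/√21.6) = 1.83 |
| 0.25 | exp(2.802/√10.125) = 2.41 | exp(2.802/√16.2) = 2.01 |
| Stated | 1.69 | 1.52 |

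The stated values are not reproduced. At the most favourable split:

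- HR 1.69 needs 115 events against 54; power with 54 is 49%.
- HR 1.52 needs 180 events against about 86; power with 86.4 is 49%.
- Solving for p(1 − p) gives [2.802/ln(1.69)]²/54 = 0.53 and [2.802/ln(1.52)]²/86.4 = 0.52. A two-group factor cannot exceed 0.25.

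Other routes do not recover the range. One-sided 5% at 50:50 gives 1.71 to 1.97. A continuous predictor per SD gives 1.35 to 1.46, and the article describes a contrast between people with and without the pattern. If the 20% attrition stated for Aim 2 also applied here (an assumption), 144 people would give 1.96 to 2.35 at 50:50.

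**The case against.** The best defence is that Aim 1 is not about prediction alone. The Hypothesis section and the results heading for the aim both speak of establishing the signature, and the cross-sectional tests serve that. The plan can be read as two steps, each with its own analysis and power statement: find the grEEG measure associated with limitations, then ask whether the pattern predicts decline. Nowhere does it say that a significant t test proves prediction. This stands, and it rules out the reading that the primary tests are the wrong tests for Aim 1. They answer one part of it.

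A reader might also infer that the t test, the correlation and the time-to-event test are three routes to a positive Aim 1, each at 5%, and so derive an inflated error rate for the aim. The document does not support that. It states 5% for the t test and the hazard ratio only, gives no level for the correlation, and contains no rule that any one significant result makes the aim positive. If each test supports only its own claim, the prediction claim keeps its 5%. Hierarchy and multiplicity are commonly left to an analysis plan, and none is shown.

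The defence does not explain why the prediction half lacks the primary label that its counterpart in Aim 2 has, nor does it rescue the hazard ratios.

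**Conclusion.** The point holds as a mismatch between label and aim: the primary analyses of Aim 1 cover the signature part only, and the one test of decline has no primary status. It does not hold as a claim that Aim 1 concerns prediction alone, or as a multiplicity finding.

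The power statement for the decline test needs correction in any case. For 180 people the detectable hazard ratio is 1.83 to 2.14 at best and 2.01 to 2.41 if a quarter have the pattern, against 1.52 to 1.69 as printed. At the printed values power is at most about 49%. These figures rest on the stated event rates, two-sided 5%, 80% power, a two-group contrast, no attrition and the assumed split. The source cited for the article's own calculation was not available, but no split brings a two-group contrast down to the printed range under this formula.

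**What to change.** In Statistical Plan Aim 1:

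1. Name the time-to-event test of ADL-PI decline by grEEG signature as the primary analysis for the claim that the signature predicts decline, at two-sided 5%.
2. Keep the t test and Pearson correlation as the cross-sectional analysis for the signature part.
3. Add a sentence saying that a cross-sectional association without a longitudinal one does not support the prediction claim.
4. In the Power Analysis, state the assumed share with the pattern and restate the detectable hazard ratio: on the inputs above, 1.83 to 2.14 at 50:50 or 2.01 to 2.41 at 25:75.

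The cost is a change of text with the same data and the same analyses. The real downside is that the test deciding the prediction claim is less powerful than the t test, and the published detectable effect becomes less favourable.

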### Neural Signature of CdF

To test whether this unique grEEG activation pattern also associates with the limitation in CdF, we dichotomized our sample in the following way: (1) compute the difference in activation between unperturbed and perturbed walking; (2) use inverse source localization techniques to estimate intracranial sources of scalp-recorded activity; (3) separate individuals with source localized to fronto-medial regions into groups of weak and strong θ synchronizers using the median; (4) separate individuals without sources in fronto-medial and with sources in sensorimotor region into groups of weak and strong β desynchronizers using the median (we chose right sensorimotor β because effects where strongest for that region and frequency: *P*=.04) [19].

Figure 4 shows preliminary findings in support of our hypothesis: Individuals characterized by a unique grEEG pattern report limitations in CdF to a higher degree.

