##### Power Analysis

With the sample size of 180 older adults who are cognitively unimpaired, we estimate that there will be 54 individuals classified with CdF limitations based on our preliminary studies. With a significance level (α) of .05, using a 2-sided 2-sample *t* test, this study achieves 80% power to detect a minimal difference of 0.5 SD in the grEEG measure between CdF limitation groups. The minimum detectable hazards ratio for CdF decline between older adults with and without unique grEEG pattern ranges from 1.52 to 1.69 (assuming event rate between 0.30 and 0.48) with a power of 0.8 and a 2-sided type I error rate of 5% [89].

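### The Aim 1 primary analysis looks for which of several grEEG measures is associated with CdF limitation, with no primary measure or error control named, while power is stated for one measure at α=.05

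*Protocol article*

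**What the plan says.** Under Statistical Plan Aim 1, Primary Analyses, the protocol article plans two-sample t tests on grEEG measures, in the plural, "to assess which grEEG measure is associated with limitations in CdF". It adds Pearson correlations between the same measures and CdF scores. It gives no number of measures, no primary one and no alpha.

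The Power Analysis for Aim 1 speaks of one measure. It takes 180 participants, of whom "we estimate that there will be 54 individuals classified with CdF limitations based on our preliminary studies". "With a significance level (α) of .05" and a two-sided t test, it states that "this study achieves 80% power to detect a minimal difference of 0.5 SD in the grEEG measure between CdF limitation groups".

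The grEEG Protocol section names two measures: 13-28 Hz (β) desynchronization over the pre- or postcentral gyrus, and 3-7 Hz (θ) synchronization over fronto-medial cortex. Walking Tasks describes two tasks, visually perturbed walking and dual-task walking. On how the preliminary sample was split, Neural Signature of CdF says: "we chose right sensorimotor β because effects where strongest for that region and frequency", with P=.04.

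**The concern.** The primary analysis is worded as a search: several candidates are tested, and the result tells which one is associated. The power statement describes a different design, one measure tested once at .05. If the plan is followed as printed, with .05 applied to every test, the chance that at least one measure looks associated by luck exceeds 5%, and the stated power no longer describes the analysis that controls that error.

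This matters because Aim 1 is meant to establish a neural signature. The t tests are its cross-sectional evidence, and incidence of the signature is the outcome for Aims 2 and 3. The preliminary work shows how easily a region and band can be picked because the effect there was largest.

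**Working it through.** **Inputs**
- Total N = 180; 54 with CdF limitation (Aim 1 Power Analysis). Without limitation: 180 − 54 = 126.
- α = .05, two-sided; power 80%; difference 0.5 SD (same paragraph).
- Measures named: 2 (grEEG Protocol). Tasks: 2 (Walking Tasks). Number of tests k: 2 for one task, 2 × 2 = 4 for both.
- Assumption: each test at .05. The document does not say so; .05 is the only alpha given for this analysis. The Pearson correlations are not counted as further tests.

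**1. The plan's own figure.** Power comes from the noncentral t distribution with 54 + 126 − 2 = 178 degrees of freedom and noncentrality d / √(1/54 + 1/126).
- √(1/54 + 1/126) = √0.02646 = 0.1627; at d = 0.5 the noncentrality is 0.5 / 0.1627 = 3.07.
- Power = 86.4% (86.7% by the normal approximation), against the stated 80%.
- The difference detectable with exactly 80% power is 0.458 SD. By the normal approximation: (1.960 + 0.842) × 0.1627 = 0.456.

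The stated 0.5 SD is therefore conservative for a single test. It agrees with the recomputed value only when that is rounded to one decimal.

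**2. Chance of at least one false-positive measure.** For k independent tests this is 1 − 0.95^k. Correlated tests were simulated as equicorrelated two-sided tests, 400,000 draws each.

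| k | independent | correlation 0.3 | correlation 0.5 | correlation 0.8 |
|---|---|---|---|---|
| 2 | 9.8% | 9.5% | 9.1% | 7.9% |
| 4 | 18.5% | 17.3% | 15.6% | 11.4% |

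The range is about 10-19% under independence, and about 8-19% allowing correlation up to 0.8.

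**3. Power with error control.** Each test is held to .05/k with 54 versus 126. This is the first and strictest step of Holm, so it is the conservative figure for any one measure.

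| k | α per test | power at 0.5 SD | detectable at 80% power | N for 80% power at 0.5 SD |
|---|---|---|---|---|
| 1 | .05 | 86.4% | 0.458 SD | – |
| 2 | .025 | 79.1% | 0.505 SD | 184 |
| 4 | .0125 | 70.9% | 0.548 SD | 216 |

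With two measures the printed claim of 80% power at 0.5 SD nearly holds. With four tests it falls short by about nine percentage points.

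**The case against.** The strongest reply is that this is a condensed article. A multiplicity rule may sit in the full protocol or analysis plan, neither of which is shown, and the Primary Analyses text never says that each test is run at .05. That stands: uncorrected testing is an inference from the power paragraph, and the absence of a correction rule is not in itself the fault. What remains is on the page: a primary analysis set up to find which of several measures is associated, next to a power statement for one.

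Second, the signature is described in advance as a directional pair, weaker β with stronger θ (Hypothesis, grEEG Protocol, Principal Findings), and the longitudinal analysis uses that pattern. A reader might infer that whichever measure reaches significance becomes the signature, so that the error rate above is the chance of a false signature. The documents do not support this. The figure is the chance that at least one component measure is falsely positive, in either direction. Counting only the predicted direction, it would be 1 − 0.975² = 4.9% for two independent tests and 1 − 0.975⁴ = 9.6% for four.

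Third, a reader might count hemispheres and pre- and postcentral sites separately, reach eight tests, and quote 1 − 0.95⁸ = 34%. The text fixes no such count. It gives the pre- or postcentral gyrus as the location of one β measure, and measures from the same recordings are unlikely to be independent.

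Fourth, choosing a region in pilot data and testing it in a new cohort is ordinary practice, and nothing says pilot participants are reused. That is fair. The pilot choice illustrates the risk but is no defect of the new study.

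**Conclusion.** The point holds in a limited form. The primary analysis selects among an unstated number of grEEG measures without naming a primary one or an error-control rule, and the power statement covers one measure. With the two measures that the text names, or four tests over both tasks, the chance of at least one false-positive measure is about 10-19% if the tests are independent, and about 8-19% allowing correlation up to 0.8. This rests on two assumptions: .05 for each test, and a count of two to four.

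The consequence for power is small with two measures (79.1% at 0.5 SD) and noticeable with four (70.9%), because the stated 80% understates the single-test power of 86.4%. The documents support neither a 34% error rate nor a chance of a false signature.

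**What to change.** In Statistical Plan Aim 1, Primary Analyses:
- Name the two hypothesised measures, fronto-medial θ and sensorimotor β, in one stated task as primary, with the β region and side fixed in advance.
- Test the two with Holm at an overall two-sided .05.
- Label other regions and the second task as secondary.

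In the Aim 1 Power Analysis, restate the difference detectable with 80% power for 54 versus 126 as about 0.51 SD (two tests). If both tasks are to stay primary, it is 0.55 SD (four tests).

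The change needs wording only, with no new participants or measurements. The cost is a stated detectable difference slightly less favourable than 0.5 SD, and secondary standing for the other task.
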